# Introduction

This study aims to determine whether protection from COVID-19 vaccination wanes after the booster dose of SARS-CoV-2 vaccines. If possible, we plan to conduct harmonised analyses across different contexts to strengthen confidence that trends in variants (VOCs) do not drive findings, increase statistical power, and allow robustness of results when adjusting for differing confounders to be assessed. A current collaboration will enable analyses to be conducted in Scotland and Brazil.

In Scotland, the primary series (two doses) mainly included Oxford-AstraZeneca (ChAdOx1) or Pfizer-BioNTech (BNT162b2). The primary series in Brazil included: ChAdOx1, CoronaVac, BNT162b2 and Ad26.COV2.S. At present, the vaccination programme in Scotland uses two mRNA vaccines as boosters: Pfizer-BioNTech (BNT162b2) and Moderna (mRNA-1273) vaccines. The vaccination programme in Brazil currently offers mainly BNT162b2 as a booster dose of a primary series with BNT162b2, ChAdOx1, Ad26.COV2.S or CoronaVac. In this study we will analyse data of BNT162b2 and ChAdOx1 as a primary series and booster with BNT162b2.

We aim to evaluate the real-world impacts of being fully vaccinated and assess whether the rate of infection and severe outcomes (deaths and hospitalisations) (RR) diminishes over time after the booster dose. e will use deidentified individual-level linked data. All data and analyses will be hosted within secure analytical environments.

# Aims and Objectives

## 2.1 Aims

To assess the relationship between time since the maximum protection following a booster dose and the risk of severe COVID-19 (hospitalisation or death). We will also assess the secondary outcomes of confirmed SARS-CoV-2 infection.

## 2.2 Objectives

By vaccine type, we seek to:

1. Estimate Odds Ratio (OR) against the composite outcome of COVID-19 hospitalisation/death of individuals with booster dose versus individuals without booster dose.
2. Estimate Odds Ratio (OR) against confirmed SARS-CoV-2 infection of individuals with booster dose versus individuals without booster dose.
3. Estimate Rate Ratio (RR) against the composite outcome of COVID-19 hospitalisation/death as a function of time post maximum effect of the booster dose of a COVID-19 vaccine.
4. Estimate RR against the separate outcomes of i) COVID-19 hospitalisation; ii) COVID-19 death as a function of time post maximum effect of the booster dose of a COVID-19 vaccine.
5. Assess if waning of protection from booster dose differs by age group, sex and being in a high-risk COVID-19 group

# Study Design

## 3.1 Study design

Objectives a) and b) will be evaluated through a test-negative design case-control study

Objective c) and d) open prospective cohort study comparing outcomes amongst vaccinated people for differing lengths of time.

## 3.2 Settings

Scotland and Brazil.

## 3.3 Population

In Scotland our main population of interest is adults who have completed a full COVID-19 vaccination schedule (typically two doses) resident in the countries. Our secondary population of interest in Scotland is all adults.

In Brazil our primary population of interest is all adults who have received a booster dose, with primary series of any available vaccine.

For the test-negative design, in both countries, we will study all adults who have received a COVID-19 RT-PCR or Rapid Antigen^^[[1]](#footnote-0)^^ test after the begin of booster dose campaign in each country (Brazil: 2021/09/15; Scotland: 2021/09/15)

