## 3.5 Inclusion/exclusion criteria

Inclusion criteria for the primary cohort:

- Receive at least two doses of BNT162b2 or ChAdOx1 before or during the study period.

Exclusion criteria for the primary cohort:

- Inconsistent vaccination records (i.e. received a second dose with no record of a first dose, received doses from different vaccine types or interval between doses of less than 14 days)
- Missing essential covariates (sex, age, geography)
- Children (under the age of 18 years)
- Hospitalization previous to the study start date
- A positive test within 28 days of the study start date

Inclusion criteria for the TND:

- Receive at least two doses of BNT162b2 or ChAdOx1 at the sample collection date.

Exclusion criteria for the TND:

- Tests within 90 days of a previous positive test
- Negative tests followed by a positive test within 7 days
- Negative tests within 14 days of a previous negative test
- Missing essential covariates (sex, age, geography)
- Children (under the age of 18 years)

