## 3.6 Sample size calculations

Based on a preliminary review of descriptive statistics in both countries, we anticipate the following numbers:

- Scotland:
  - ChAdOx1:
  - BNT162b2:
- Brazil
  - ChAdOx1: 10 million individuals with booster from 49M with 2 doses
  - BNT162b2: 5 million individuals with booster from 28M with 2 doses

If adequate numbers are not available for statistical analysis for a specific vaccine, we will not progress that analysis and censor individuals who receive that vaccine.

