# Statistical Analyses

### 5.1.1 Exposures of interest

###

Our primary exposure will be receipt of a COVID-19 vaccine booster, with categories to include time since receipt of a booster dose. In this setting, a patient’s vaccination status (exposure) will change over time, as a time-varying exposure.

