### 5.1.5 Analytical techniques

We will commence analysis by conducting descriptive analyses to visually inspect trends in vaccination delivery, age-specific COVID-19 hospitalisations and COVID-19 deaths, including by age group and sex. This will include checking the number of people who have received two doses and the length of follow-up available following the second dose by vaccine type. Including plotting Lexis diagram to afford for the correlated structure of the data (Calendar Time/Length of Follow-up)

For the analysis consisting of individuals with at least two doses, we will stratify the cohort based on the month of the second dose of each individual. The vaccination status will be classified as:

- Second dose:
  - <2 weeks
  - 2-9 weeks
  - 10-19 weeks
  - ≥20 weeks without a booster dose [Reference Period]
- Booster dose:
  - <2 week
  - 2-4 weeks
  - 5-8 weeks
  - 9-12 weeks
  - ≥13 weeks

This variable will be used to fit a Poisson regression to obtain rate ratios (RRs) and their 95% confidence intervals (CIs). If we observe overdispersion, we will consider using Negative Binomial regression models or Poisson with robust standard errors. Models will be adjusted for the relevant confounders above, including a set of dummy variables for calendar week.

The models will be fit to a dataset with all events and a random sample, without replacement, of 100 individuals per event (for hospitalisation and death, 10 for positive tests). The sample weights will be calculated to represent the sampling fraction, thus ensuring the correct calculation of the person-years at risk for the whole population.

The primary analysis for the test negative will be on individuals who are symptomatic at the time of test and the date of symptom onset is 0-10 days before the test. We will then establish the number of weeks post-vaccination for the cases and controls calculated as time between sample collection date and vaccine dose. The odds' ratio will be calculated using a logistic regression. Adjusted for: race/ethnicity, comorbidities, dummy variables for calendar week, age (five-year bands), sex. Controls will be defined based on a negative test.

We will also construct a propensity score to be tested among those in the primary cohort and use this as an inverse propensity weight.

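### Section 3.3 restricts Brazil's primary population to boosted adults, contradicting the two-dose cohort and unboosted reference of sections 3.5 and 5.1.5; if followed, it would bias the Brazil rate ratios

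*SAP*

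**What the plan says.** - **Section 3.3, Brazil:** "In Brazil our primary population of interest is all adults who have received a booster dose, with primary series of any available vaccine".
- **Section 3.3, Scotland:** "In Scotland our main population of interest is adults who have completed a full COVID-19 vaccination schedule (typically two doses"). No booster is needed.
- **Section 3.5, primary cohort, not split by country:** "Receive at least two doses of BNT162b2 or ChAdOx1 before or during the study period". No booster is needed.
- **Section 3.6, Brazil:** boosted people are counted out of all two-dose people, for example "BNT162b2: 5 million individuals with booster from 28M with 2 doses". For ChAdOx1 the figures are 10 million out of 49M.
- **Section 5.1.1:** "a patient’s vaccination status (exposure) will change over time, as a time-varying exposure".
- **Section 5.1.5, analysis set:** "For the analysis consisting of individuals with at least two doses, we will stratify the cohort based on the month of the second dose". The reference category of the Poisson model is "≥20 weeks without a booster dose [Reference Period"].
- **Introduction:** the primary series to be analysed are BNT162b2 and ChAdOx1 only.

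The test-negative design has its own population in 3.3 (tested adults, both countries) and its own two-dose criterion in 3.5.

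**The concern.** Section 3.3 gives Brazil a population selected on having had a booster, while the cohort model compares boosted time with time spent without one. A person who dies unboosted can never join a population of booster recipients. The reference time of such a population is therefore survivor time.

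The cohort serves objectives 3 and 4, and its main outcome is the primary composite of COVID-19 hospitalisation or death. A reference rate that is too low pushes the booster rate ratio up, so real protection is understated or the booster looks harmful.

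There is a second conflict in the same sentence. It admits every primary series in use, and the Introduction lists four for Brazil, whereas the Introduction's analysis statement and section 3.5 allow two.

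**Working it through.** The SAP gives no power, event or effect figure on this point, so there is nothing of its own to reproduce. The check has three parts.

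**1. Can the sections be applied together?** Yes, and that is the difficulty. A boosted adult with a primary series of either named vaccine also meets the two-dose criterion of 3.5. Applying 3.3 and 3.5 jointly therefore yields ever-boosted people only. These people still contribute time after dose 2 and before the booster, so every category in 5.1.5 can be filled and the model will run without warning. Time-varying coding (5.1.1) puts person-time in the right category within the cohort. It does not undo selection of the cohort on a later event.

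**2. How many people are involved?** Inputs are the Brazil counts in section 3.6.

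| Primary series | Two doses | Boosted | Boosted share | Not boosted |
|---|---|---|---|---|
| ChAdOx1 | 49M | 10M | 10/49 = 20.4% | 39M |
| BNT162b2 | 28M | 5M | 5/28 = 17.9% | 23M |
| Both | 77M | 15M | 15/77 = 19.5% | 62M (62/77 = 80.5%) |

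**3. Which way, and how far, would the rate ratio move?** A simulation with a true rate ratio of 1 shows this. Only the uptake comes from the SAP (15/77). The rest are assumptions: 4 million people followed for 26 weeks from week 20 after dose 2, constant hazards, and an event rate of 0.1% per week, set high for precision. The weekly booster hazard is −ln(1 − 15/77)/26 = 0.0083. Let q be the booster hazard after an event relative to before it. Death is q = 0, and q = 1 means that the event has no effect on later uptake.

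| q | Reference events, ever-boosted only | Boosted events | Rate ratio, ever-boosted only | Rate ratio, all two-dose people |
|---|---|---|---|---|
| 0 | 0 | 10,269 | infinite | 0.99 |
| 0.25 | 2,590 | 10,230 | 3.68 | 0.99 |
| 0.5 | 5,084 | 10,238 | 1.89 | 1.00 |
| 0.75 | 7,360 | 10,366 | 1.32 | 1.00 |
| 1 | 9,828 | 10,204 | 0.98 | 0.99 |

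The ever-boosted results lie close to 1/q (4, 2, 1.33 and 1). This is expected, because about a share q of pre-booster events stays visible in the reference. The same reasoning applies to the composite. If a share f of pre-booster events is fatal before any booster, and the remaining events do not affect uptake, the null rate ratio is about 1/(1 − f). It exceeds 1 whenever f is above zero. The documents give neither f nor q.

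**The case against.** The strongest reply is that 3.3 names a population of interest in general terms, whereas eligibility is set in 3.5, which requires no booster and makes no country split. Sections 3.6, 5.1.1 and 5.1.5 all fit that reading. Under it, the reference is neither empty nor immortal, and the simulation returns 0.99 to 1.00. A boosted-only population also has a coherent use: objectives 3 and 4 concern time since the booster's maximum effect, section 3.1 compares vaccinated people by length of time, and the waning trend test starts at 14–27 days.

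Much of this stands, and it rules out several stronger readings that a reader might draw from 3.3:

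- **That the Brazil reference is empty or immortal, with zero deaths and an undefined death rate ratio.** This holds only if 3.3 overrides 3.5 and 5.1.5, and the SAP does not say that it does.
- **That the composite rate ratio would be undefined.** It need not be. People can be admitted and boosted later, so admissions can occur in the reference even in an ever-boosted cohort. Bias from non-fatal admissions could be nil (q = 1).
- **That the 62M are people who never get a booster.** They were unboosted at a preliminary review, the cohort is open, and the counts precede the exclusions in 3.5.
- **That all booster estimates for Brazil are at risk.** The odds ratios of objectives 1 and 2 come from the separately defined test-negative population.
- **That a promise of harmonised populations is broken.** The Introduction offers harmonised analyses only where possible, and 3.5 sets one criterion for both countries.

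The reply fails in two respects. The SAP gives no order of precedence, and 3.3 and 3.5 can be combined without visible conflict. Comparing only times since booster would need no unboosted group, but 5.1.5 sets one.

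**Conclusion.** The Brazil sentence in 3.3 is wrong as written. On the booster requirement it contradicts 3.5 and 5.1.5 and does not fit the counts in 3.6. On the primary series it contradicts 3.5 and the Introduction. The harm is conditional on an analyst applying 3.3 to the cohort:

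- With entry at the booster, there is no reference time.
- With pre-booster time kept, reference deaths are impossible and the composite loses every event that is fatal before a booster. The rate ratio is then biased upward.
- About 62M of 77M two-dose people would be left out, on preliminary counts.

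The direction follows from the selection itself. The simulated sizes (1.32 to 3.68 for q from 0.75 down to 0.25) are illustrations that rest on the stated assumptions and do not predict this study's results.

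**What to change.** Replace the Brazil sentence in section 3.3 with:

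*In Brazil the primary population for the cohort is all adults who have completed two doses of ChAdOx1 or BNT162b2, with or without a booster.*

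Add that booster status enters as the time-varying exposure of section 5.1.1 and that nobody is selected on later booster receipt. The new sentence also settles the primary series in line with 3.5 and the Introduction.

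The cost is a change of wording. Section 3.4 describes the Brazilian vaccination register as covering the whole population, so no new data are needed. Section 6.2 commits to publishing the plan before the main analyses, so the change should be made before then.

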## 3.4 Data sources

In Scotland, we will draw on the following databases:

- Primary care data: General Practices (n=940) for information on demographics, other population characteristics and vaccination data.
- Vaccination data: Vaccines administered in national vaccination centres and data available via the Turas Vaccination Management Tool (TVMT).
- Secondary care data: Hospital admissions through the Scottish Morbidity Record (SMR) and Rapid Preliminary Inpatient Data (RAPID).
- Laboratory test data: RT-PCR laboratory confirmed SARS-CoV-2 infection and data available via the Electronic Communication of Surveillance in Scotland (ECOSS) database.
- Mortality data from National Records Scotland (NRS)

Equivalent datasets will be used for other UK/international countries. In Brazil, we will analyse deterministically linked data provided by the Ministry of Health:

- COVID-19 vaccination (SI-PNI): Dates and types of vaccination administered, primary reason for vaccination, indigenous status, pregnancy status.
- Acute Respiratory Infection Suspected Cases (eSUS-Notifica): register of suspected and confirmed COVID-19 cases
- Severe Acute Respiratory Infection/Illness (SIVEP-Gripe): contains all hospitalisations and deaths due to severe acute respiratory illnesses, including COVID-19.

The above three databases all have whole population coverage, with returns from both public and private healthcare systems. However, data quality may vary geographically (typically data quality is better in the south of Brazil). Testing capacity has also improved over the course of the pandemic, but most improvements occurred prior to the vaccination programmes starting. In addition to the above datasets, it may be possible in the future to obtain linkage to general hospital records for patients treated within the public healthcare system (covering approximately 70% of hospitalisations in Brazil).

## 3.5 Inclusion/exclusion criteria

Inclusion criteria for the primary cohort:

- Receive at least two doses of BNT162b2 or ChAdOx1 before or during the study period.

Exclusion criteria for the primary cohort:

- Inconsistent vaccination records (i.e. received a second dose with no record of a first dose, received doses from different vaccine types or interval between doses of less than 14 days)
- Missing essential covariates (sex, age, geography)
- Children (under the age of 18 years)
- Hospitalization previous to the study start date
- A positive test within 28 days of the study start date

Inclusion criteria for the TND:

- Receive at least two doses of BNT162b2 or ChAdOx1 at the sample collection date.

Exclusion criteria for the TND:

- Tests within 90 days of a previous positive test
- Negative tests followed by a positive test within 7 days
- Negative tests within 14 days of a previous negative test
- Missing essential covariates (sex, age, geography)
- Children (under the age of 18 years)

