### 5.1.4 Potential effect modifiers

Stratification into different population:

- Primary vaccination schedule (2 doses): ChAdOx1, BNT162b2
- Age group (18-49,50-64, 65+ years)
- Period of which variant (Delta or Omicron)
- Additional, given that VE may differ between those with multiple underlying medical conditions, that are related to serious COVID-19, we will stratify analyses by COVID-19 risk group when data allow. We will also consider stratifying analyses by vaccine type and calendar time (to reflect different dominant variants present in the country).

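### The cohort exclusion for mixed vaccine types is not limited to the first two doses, so as written it removes ChAdOx1-primed people boosted with BNT162b2

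*SAP*

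**What the plan says.** Section 3.5 admits to the primary cohort people who "Receive at least two doses of BNT162b2 or ChAdOx1 before or during the study period". It then excludes those with inconsistent vaccination records. A parenthesis opened by i.e. defines these as a second dose without a recorded first dose, or a person who "received doses from different vaccine types or interval between doses of less than 14 days". The first element names dose numbers; the mixed-type element does not, and no exception is made for the booster.

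Other sections describe what the cohort must contain:

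- Introduction, on scope: "In this study we will analyse data of BNT162b2 and ChAdOx1 as a primary series and booster with BNT162b2".
- Introduction, on boosters in use: "At present, the vaccination programme in Scotland uses two mRNA vaccines as boosters" (BNT162b2 and mRNA-1273), and "The vaccination programme in Brazil currently offers mainly BNT162b2 as a booster dose".
- Section 3.6, on anticipated numbers in Brazil: "ChAdOx1: 10 million individuals with booster from 49M with 2 doses", and 5 million boosted of 28 million for BNT162b2.
- Section 5.1.4, first stratification factor: "Primary vaccination schedule (2 doses): ChAdOx1, BNT162b2".

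Section 3.1 assigns the third and fourth objectives of section 2.2 (lettered c and d there) to the cohort, and the first two to the test-negative study. Section 5.1.1 treats vaccination status as time-varying.

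**The concern.** The study names two regimens: ChAdOx1 or BNT162b2 as the primary series, each followed by BNT162b2. The first mixes vaccine types by construction. An exclusion for mixed types that is not limited by dose number removes it from the cohort, which is the design assigned to the question of waning after the booster.

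A second effect comes from timing. The rule excludes the whole person, but what triggers it may be a booster given during follow-up. Unboosted time already accrued is then removed because of a later event. That conflicts with a time-varying exposure, under which the same person should contribute first unboosted and then boosted time.

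**Working it through.** The SAP gives anticipated counts only, with no power calculation to reproduce. The check is a comparison of sections plus simple proportions.

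**Step 1: apply the section 3.5 rule to each dose history that the Introduction describes.**

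| Primary series | Booster | Different types across all doses? | Cohort status as written |
|---|---|---|---|
| ChAdOx1 ×2 | none | no | kept |
| ChAdOx1 ×2 | BNT162b2 | yes | excluded |
| BNT162b2 ×2 | none | no | kept |
| BNT162b2 ×2 | BNT162b2 | no | kept |
| BNT162b2 ×2 | mRNA-1273 (Scotland) | yes | excluded |

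The second row is one of the two regimens the Introduction says will be analysed.

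**Step 2: size in Brazil (section 3.6).**

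- Anticipated boosted people: 10M + 5M = 15M.
- Share that is ChAdOx1-primed: 10 / 15 = 66.7%.
- Boosted share within each primary series: 10 / 49 = 20.4% for ChAdOx1 and 5 / 28 = 17.9% for BNT162b2.
- If all 10M had a BNT162b2 booster, the rule as written leaves 15M − 10M = 5M boosted people, all BNT162b2-primed. The ChAdOx1 stratum keeps 49M − 10M = 39M people, none of them boosted.
- With the rule limited to doses 1 and 2, all 15M stay eligible under this criterion.

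The 10M loss is an upper bound. Section 3.6 does not give the booster product, and the Introduction says boosters in Brazil are mainly BNT162b2. Any ChAdOx1-primed person boosted with ChAdOx1 would be kept.

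**Step 3: Scotland.** The counts in section 3.6 are blank, so no share can be computed. Only mRNA boosters are described there, so under that programme every boosted ChAdOx1-primed person would meet the exclusion.

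**Step 4: which objectives are affected.**

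- Objectives 3 and 4 (rate ratios by time since booster, by vaccine type): the ChAdOx1 stratum has no BNT162b2-boosted person-time, so none of the booster categories in section 5.1.5 can be estimated for that regimen.
- Objective 5 (differences in waning by age, sex and risk group): section 3.1 gives it no design. Only a cohort-based part would be lost.
- Objectives 1 and 2: the test-negative criteria in section 3.5 contain no mixed-type exclusion, so these are unaffected.

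**Step 5: pre-booster person-time.** In the two excluded rows the person's unboosted time is deleted as well. That includes time in the reference category of section 5.1.5 (unboosted, from 20 weeks after dose two). For ChAdOx1 with BNT162b2 this adds little, because no booster rate ratio remains to be distorted. For the BNT162b2 stratum in Scotland it does matter: booster rate ratios are still estimated there, but the reference has lost the time of people later boosted with mRNA-1273. The SAP gives no count of such people, so the size is unknown.

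**The case against.** The best defence is that the authors meant mixed types within the two-dose primary series. The bullet concerns inconsistent records, its first element is about doses one and two, and a booster that the programme itself offers is hardly an inconsistent record. The Introduction, section 3.6 and section 5.1.4 make sense only on that reading. An analyst who applied the rule to all doses would also see an empty booster group at the descriptive stage.

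This is probably what was intended, and it makes the defect one of wording, not a deliberate design decision. It does not remove the defect. No text limits the rule to the primary series, and the inclusion criterion of at least two doses brings a third dose within its scope. That other sections need the narrower reading confirms the contradiction. The SAP is to be published before the main analyses and is meant to support harmonised work in two countries, so two teams could build different cohorts from the same sentence.

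The defence also limits the consequences. A reader might infer that the ChAdOx1-plus-BNT162b2 regimen is lost to the whole study, or that objective 5 fails entirely. Neither follows: the test-negative study keeps the regimen and also classifies weeks since vaccination, and objective 5 is not tied to the cohort. A reader might also infer that the ChAdOx1 booster estimates would be biased by a reference group selected for never being boosted. As written, there would be no BNT162b2-booster estimate in that stratum to bias.

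**Conclusion.** The point holds for the primary cohort. As written, the exclusion in section 3.5 contradicts the Introduction and sections 3.6 and 5.1.4. It makes objectives 3 and 4, and any cohort-based part of objective 5, inestimable for a BNT162b2 booster after ChAdOx1. In Brazil the loss is at most 10M of 15M anticipated boosted people (66.7%). That bound assumes every ChAdOx1-primed booster there was of a different type, and it uses the SAP's counts before other exclusions. For Scotland the conclusion is qualitative and assumes that the described mRNA-only programme applies. Deletion of pre-booster time is a further, unquantified effect, relevant mainly to BNT162b2-primed people boosted with mRNA-1273. The correction is needed before the cohort is built, because the stated rule followed exactly gives a wrong result.

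**What to change.** Reword the mixed-type element in section 3.5 to *first and second doses of different vaccine types*, so that a BNT162b2 booster after either primary series is retained. This alone resolves the contradiction.

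As a secondary addition, state that people who receive another booster product contribute person-time until that dose and are censored then, and are not excluded entirely. Section 3.6 already provides for censoring by vaccine, but only where numbers are too small to analyse, so it does not settle this case.

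The cost is one or two lines of SAP text and a matching change in the cohort code. Vaccine type, dose and date are already listed for both countries in Tables 1 and 2, so no new data are needed.

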### 5.1.7 Sensitivity analysis

We will consider exploring the impact of alternative approaches to classifying the start of the exposed period (e.g. from day 7 after completion of the vaccination schedule), classifying COVID-19 hospitalisation based on primary diagnosis (rather than any diagnostic position), using only individuals with five days of fewer from symptom onset to test (reducing the risk of false-negative) and statistical adjustment for people with previous COVID-19 infection (rather than excluding them).

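### In the primary test-negative analysis a narrow gap lets one illness supply both a control and a case; the effect on the odds ratios is very small and a same-onset-date clause closes it

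*SAP*

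**What the plan says.** Section 3.5 lists three TND exclusions that depend on earlier or later tests:

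- A look-back that acts once a person has tested positive: "Tests within 90 days of a previous positive test"
- A look-forward that removes likely false negatives, the rule at issue here: "Negative tests followed by a positive test within 7 days"
- A spacing rule for repeated negatives: "Negative tests within 14 days of a previous negative test"

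Section 5.1.5 restricts the primary TND analysis to people who are symptomatic when tested and for whom "the date of symptom onset is 0-10 days before the test". On controls it says "Controls will be defined based on a negative test". The SAP states no limit of one test per person or per illness.

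Section 5.1.7 names, as something that may be explored, a sensitivity analysis "using only individuals with five days of fewer from symptom onset to test (reducing the risk of false-negative".

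**The concern.** A negative test soon followed by a positive is a likely false negative, and dropping it keeps infected people out of the control group. The look-forward for this is 7 days, but tests are accepted up to 10 days after onset. Two tests of the same illness that are 8, 9 or 10 days apart therefore escape the exclusion. The early negative stays as a control and the later positive enters as a case, for the same person with nearly the same vaccination history.

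An infected person counted as a control brings the exposure pattern of cases into the control group. That moves the booster odds ratios for Objectives 1 and 2 towards 1. At stake is a slight understatement of booster protection; its existence is not in doubt on this account.

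**Working it through.** The SAP gives no figure to reproduce here, so the check applies the stated rules to every possible case and then sizes the bias under stated assumptions.

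**1. Which same-illness pairs survive**

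Inputs: onset window 0-10 days (section 5.1.5); look-forward 7 days, look-back after a positive 90 days, repeat-negative window 14 days (all section 3.5).

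Let the negative fall on day a and the positive on day b after one onset, with 0 ≤ a < b ≤ 10. There are 11 × 10 / 2 = 55 such pairs, and a gap of g days can occur in 11 − g ways.

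- With 7 days read as inclusive, gaps of 8, 9 and 10 survive: 3 + 2 + 1 = 6 pairs, namely (0,8), (0,9), (0,10), (1,9), (1,10), (2,10). The rule removes the other 49.
- With 7 days read as exclusive, the 4 pairs with gap 7 survive as well, giving 10.

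**2. Whether another rule catches them**

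- The 90-day rule acts only on tests taken after a positive, so it cannot remove an earlier negative.
- The 14-day rule drops the later of two negatives and keeps the earlier. With negatives on days 0 and 4 and a positive on day 9, the day-4 negative goes, but the day-0 negative and the day-9 positive both stay.
- With onset to test limited to 5 days or fewer there are 6 × 5 / 2 = 15 pairs, none more than 5 days apart, so none survives.
- With the 0-10 day window kept, an inclusive look-forward of 9 days still leaves (0,10); one of 10 days leaves none.

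**3. Size of the bias**

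Assumptions, none from the SAP: 40% of true controls are boosted; a share f of the analysed controls are such false negatives; these have the exposure distribution of cases.

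- Case odds of being boosted = OR × 0.40/0.60, which gives the boosted share p among cases.
- Boosted share among analysed controls: m = (1 − f) × 0.40 + f × p.
- Observed OR = case odds ÷ [m/(1 − m)].

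Worked example, OR 0.50 and f = 1%: case odds = 0.5 × 0.6667 = 0.3333, so p = 0.25; m = 0.99 × 0.40 + 0.01 × 0.25 = 0.3985; control odds = 0.3985/0.6015 = 0.6625; observed OR = 0.3333/0.6625 = 0.503.

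| f | True OR 0.50 becomes | Relative shift | True OR 0.20 becomes | Relative shift |
|---|---|---|---|---|
| 0.2% | 0.5006 | 0.1% | 0.2005 | 0.2% |
| 1% | 0.503 | 0.6% | 0.202 | 1.2% |
| 2% | 0.506 | 1.3% | 0.205 | 2.4% |
| 5% | 0.516 | 3.2% | 0.212 | 6.1% |

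For small f the relative shift is about f × (0.40 − p)/(0.40 × 0.60). This is 0.625 f for OR 0.50 (p = 0.25) and 1.18 f for OR 0.20 (p = 0.118). The shift stays below 1% for f up to about 1.6% and 0.8% respectively.

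**The case against.** A reader might infer that the 7-, 10- and 14-day windows contradict each other. They do not. One limits the delay from onset to test, one the gap from a negative to a later positive, and one the spacing of repeat negatives. All three can be applied together, and the SAP nowhere says that they must be equal.

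A reader might also infer that the 7-day rule fails at its purpose, or that 6 of 55 is a contamination rate. Neither is supported. The rule removes most same-illness pairs, and the count is of possible day combinations, not of participants. The surviving pairs need a test in the first days of illness and another more than a week later.

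Nor does it follow that the look-forward must become a flat 10 days. A negative followed by a positive 8-10 days later can be a true negative from another illness and then a new infection. A longer flat window removes such controls too, which selects controls on a later outcome. That is a fair argument for keeping 7 days as the general rule.

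Two further points stand. No look-forward rule reaches an infected person who tests negative and is never retested. And the SAP has not overlooked false negatives: its 5-day analysis contains no such pairs. That analysis is optional, however, and leaves the primary analysis as it is.

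What remains after all this is the gap itself. On the stated rules one illness can still be counted on both sides of the comparison, and closing the gap does not require a longer flat window.

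**Conclusion.** The point holds as a small refinement. In the primary TND analysis, a negative on days 0-2 and a positive on days 8-10 of one illness both survive the stated exclusions. On the exclusive reading of 7 days the gap is slightly wider.

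The bias is towards 1 and probably well under 1% in relative terms. That judgement assumes that f lies near the low end of the range shown, because the gap is narrow. The SAP gives no repeat-test frequency, so f cannot be computed, and nothing in the document supports a value as high as 5%. The sizes also rest on the assumed 40% boosted among controls. No conclusion under Objective 1 or 2 is shown to change. Priority: lowest, nice to have.

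**What to change.** In the TND exclusions of section 3.5, keep the 7-day rule and add a clause: also exclude a negative test when a later positive test in the same person has the same recorded symptom-onset date. No recorded illness then contributes both a control and a case. Unlike a longer flat window, the clause leaves in place a negative from a separately recorded illness. State at the same time whether 7 days is inclusive.

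A flat 10-day look-forward, inclusive, may be run as a sensitivity analysis. It needs only test dates, so it also covers pairs whose two onset dates were recorded differently.

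The cost is a line of SAP text, a line of code and a very small number of controls. The clause needs an onset date for both tests. Tables 1 and 2 do not list that item by name, but the primary analysis in section 5.1.5 already depends on it.
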